## Sample size

Prior data indicate that in determining patients' knowledge level with regard to the use of intranasal steroids for AR treatment, the mean score of adults with adequate knowledge about allergic rhinitis treatment among controls is estimated to be 1.39 (SD:0.71), and the estimated true mean score of adequate knowledge for interventional subjects is 1.70 (SD: 0.58) assuming 77 participants in each group (Retinasekharan et al., 2021). By using the G-power calculator, this study will need 67 interventional participants and 67 control participants to be able to reject the null hypothesis that the mean scores of the interventional

and control groups are equal with probability (power) 0.8. The Type I error probability associated with this test of this null hypothesis is 0.05. The calculation is shown below:-

Sample size estimation for the mean difference of knowledge level between groups

Intervention group

Mean score: 1.70

Standard Deviation: 0.58

Control group

Mean score: 1.39

Standard Deviation: 0.71

Pooled standard deviation

$$\begin{aligned} \text{Pooled } SD &= \sqrt{\frac{(n_1 - 1) \times SD_1^2 + (n_2 - 1) \times SD_2^2}{n_1 + n_2 - 2}} \\ &= \sqrt{[(77-1) \times 0.71^2 + (77-1) \times 0.58^2] / (77+77-2)} \\ &= 0.648267 \end{aligned}$$

Results of the G-power calculator:

F tests - ANOVA: Repeated measures, between factors

Analysis: A priori: Compute required sample size

|                                     |             |
|-------------------------------------|-------------|
| Input: Effect size f                | = 0.2005347 |
| α err prob                          | = 0.05      |
| Power (1-β err prob)                | = 0.80      |
| Number of groups                    | = 2         |
| Number of measurements              | = 3         |
| Correlation among repeated measures | = 0.5       |
| Output: Noncentrality parameter λ   | = 8.0830473 |
| Critical F                          | = 3.9128750 |
| Numerator df                        | = 1.0000000 |
| Denominator df                      | = 132       |
| Total sample size                   | = 134       |
| Actual power                        | = 0.8057571 |

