 527 Standard Deviation: 2.84  
 528 n=16; reference: (Feng et al., 2017)  
 529  
 530 Control group  
 531 Mean score: 76.62  
 532 Standard Deviation: 2.848386  
 533 n=13; reference: (Feng et al., 2017)  
 534  
 535 Pooled Standard Deviation:

$$536 \quad Pooled\ SD = \sqrt{\frac{(n_1 - 1) \times SD_1^2 + (n_2 - 1) \times SD_2^2}{n_1 + n_2 - 2}}$$

537 Pooled standard deviation  
 538 =  $\sqrt{[(16-1) \times 2.84^2 + (13-1) \times 2.848386^2] / (16+13-2)}$   
 539 = 2.843730

541 Results of the G-power calculator:

542 **F tests - ANOVA:** Repeated measures, between factors

543 **Analysis:** A priori: Compute required sample size

544 **Input:** Effect size f = 3.0289576

545 α err prob = 0.05

546 Power (1-β err prob) = 0.80

547 Number of groups = 2

548 Number of measurements = 3

549 Corr among rep measures = 0.5

550 **Output:** Noncentrality parameter λ = 55.0475049

551 Critical F = 18.5128205

552 Numerator df = 1.0000000

553 Denominator df = 2.0000000

554 Total sample size = 4

555 Actual power = 0.9350969

556

557 A study mapping the naso-ocular symptom scores to EQ-5D-5L utility values was referred to  
 558 in order to obtain the input of mean scores and standard deviation to estimate the sample  
 559 size required to compare patients' QoL between two groups. The EQ-5D-5L utility values in  
 560 mean and standard deviation were corresponding to the disease severity in AR patients,  
 561 where the utility values of  $1.000 \pm 0.000$ ,  $0.943 \pm 0.085$ ,  $0.909 \pm 0.095$ ,  $0.849 \pm 0.142$ , and  
 562  $0.767 \pm 0.175$  were corresponding to none, mild, moderate, severe, and most severe groups  
 563 (Kumanomidou et al., 2022). In this study, patients with moderate to severe allergic rhinitis  
 564 will be recruited for control and interventional groups, and the aim of the intervention is to  
 565 improve the symptoms, if not totally absence of symptoms, at least the mild disease state.  
 566 Assuming that the control group patients would remain in the disease status of moderate to

severe and the intervention group would achieve mild disease status, the EQ-5D-5L utility values corresponding to moderate ( $0.909 \pm 0.095$ ) and mild ( $0.943 \pm 0.085$ ) were selected to simulate the mean utility score of control and intervention, respectively.

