The G-Power sample size calculator is used, and by setting the function of a repeated-measure ANOVA statistical test, the probability (power) at 0.8, the Type I error probability associated with this test of this null hypothesis at 0.05, and the effect size at 0.1885976, the sample size of 70 is calculated for each group as shown in the formulation of the calculation below.

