#### Sample size estimated using G-power calculator:

**F tests** - ANOVA: Repeated measures, between factors

**Analysis:** A priori: Compute required sample size

|                |                           |              |
|----------------|---------------------------|--------------|
| Input:  | Effect size f             | = 0.3244754  |
|                | α err prob                | = 0.05       |
|                | Power (1-β err prob)      | = 0.80       |
|                | Number of groups          | = 2          |
|                | Number of measurements    | = 4          |
|                | Corr among rep measures   | = 0.5        |
| Output: | Noncentrality parameter λ | = 8.4227428  |
|                | Critical F                | = 4.0426521  |
|                | Numerator df              | = 1.0000000  |
|                | Denominator df            | = 48.0000000 |
|                | Total sample size         | = 50         |
|                | Actual power              | = 0.8115763  |

Therefore, a sample size of 25 are required for each group.

While there is no reported raw data for variance or partial eta-squared that is required to generate the effect size for determining the within group mean difference in symptom control and quality of life, a rule of thumb is used to determine the magnitude of the effect size. Generally, three different effect sizes can be generated from the different levels of partial eta-squared when using the rule of thumbs. 0.01 is meant for a small treatment effect, 0.06 is for medium, and 0.14 is for large effect size (Cohen, 1988). For this study, we estimate a small effect in order to yield the highest number of samples, and hence 0.01 is selected for partial eta-squared in order to generate an effect size. The G-power sample size calculator is used by setting the probability (power) at 0.8, the Type I error probability associated with this

test of this null hypothesis at 0.05, and the function of repeated measures, an effect size of 0.1005038 within factors ANOVA analysis. The total sample size calculated is 138, with 69 samples required for each group. The sample size calculation is shown below.

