## **Statistical analysis**

An intention-to-treat analysis will be used to include all of the patients who were assigned to each group after randomization. The data analysis will be done using SPSS version 20.0. Descriptive data will be expressed as mean and standard deviation (SD) if the data is normally distributed, or median and interquartile range (IQR) if the data is not normally distributed. Categorical data will be presented in frequency and percentage.

To determine the knowledge level, The “yes” answer will be given a score of two, the “no” answer will be given a zero score, and “not sure” will be given a score of one (Retinasekharan et al., 2021). The outcome will be presented in mean score and standard deviation for each group. Each question will be analysed separately. The knowledge levels will be assessed at baseline, Day 120 $\pm$ 7 and on Day 180  $\pm$ 7. Between-group comparisons will be analysed using Two-way repeated measure ANOVA to compare mean score different between two groups. Meanwhile, the two-way repeated measures ANOVA will show the findings for the within-group comparison. A P-value of < 0.05 will be considered statistically significant.

The Total Nasal Symptom Score (TNSS) is the sum of scores for each of nasal congestion, sneezing, nasal itching, and rhinorrhoea at each time point, using a four-point scale (0–3), where 0 indicates no symptoms, a score of 1 for mild symptoms that are easily tolerated, a

score of 2 for awareness of symptoms that are bothersome but tolerable, and a score of 3 is reserved for severe symptoms that are hard to tolerate and interfere with daily activity. A higher score indicates the more severe the symptoms are, and the main outcome of TNSS will be generated as a mean and standard deviation. A mean score will be calculated separately for the past 12 hours and past 2 week. A two-way repeated measure ANOVA analysis will be employed to determine the mean difference between the scores of the control group and the interventional group in order to determine the overall effectiveness of the intervention. Within-group comparisons will be shown as part of the outcome of the two-way repeated measures ANOVA. A value of  $P < 0.05$  is considered statistically.

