In the determination of self-reported medication adherence, a two-way repeated measure ANOVA analysis will be used to compare the between-group differences for the mean adherence rate of number of doses of intranasal corticosteroid. It will be calculated as number of doses taken by the participants divided by the total number of doses prescribed that should be taken on regular basis. Meanwhile, the two-way repeated measures ANOVA will show the findings for the within-group comparison. A value of  $P < 0.05$  is considered statistically significant.

The participants' quality of life will be presented as a mean score and standard deviation for responses in EQ-5D-5L utility index scores. The index score will be generated by using the EQ-5D-5L index calculator for Malaysia upon getting permission from the originator (copyright holder) (Shafie et al., 2019). EQ-5D VAS will be generated in the form of a mean score and standard deviation. A two-way repeated measure ANOVA analysis will be employed to determine the mean difference between the scores of the control group and the interventional group. Within-group findings will be obtained from the analysis of two-way repeated measure ANOVA. A value of  $P < 0.05$  is considered statistically significant.

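### The sample size powers a group effect averaged over all visits, Day 0 included; with no baseline difference, EQ-5D utility, which sets 70 per arm, has about 0.56 power, not 0.80

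*Combined protocol and SAP*

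**What the plan says.** In the Sample size section, each between-group run is headed "F tests - ANOVA: Repeated measures, between factors", with numerator df 1 and a correlation of 0.5. On error rates the section states: "The Type I error probability associated with this test of this null hypothesis is 0.05". The number of measurements is 4 for TNSS, EQ-5D utility and EQ-5D VAS, and 3 for knowledge and adherence.

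Utility drives the trial: "the effect size at 0.1885976, the sample size of 70 is calculated for each group as shown". Its difference is a post-treatment one. Controls are assumed to stay moderate to "severe and the intervention group would achieve mild disease status, the EQ-5D-5L utility values corresponding to moderate" (0.909) and mild (0.943) stand for the control and intervention arms.

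Table 3 places TNSS and quality of life at Day 0, 60, 120 and 180, and knowledge at Day 0, 120 and 180. Adherence has no Day 0 value.

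For knowledge, the Statistical analysis section reads: "Between-group comparisons will be analysed using Two-way repeated measure ANOVA to compare mean score different between two groups". For quality of life, it reads: "A two-way repeated measure ANOVA analysis will be employed to determine the mean difference between the scores of the control group and the interventional group". The TNSS paragraph adds that this is done "in order to determine the overall effectiveness of the intervention". No baseline covariate, group-by-time test or post-baseline contrast is named.

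For the within-group aim: "The total sample size calculated is 138, with 69 samples required for each group".

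**The concern.** A between-factors test with one numerator df compares the arms on each patient's mean over all measurements. The counts of 4 and 3 match the schedule only if Day 0 is included. All patients enter with moderate to severe disease and are randomised 1:1, so the expected Day 0 difference is zero. The planned difference can hold at three of four visits at most, or two of three for knowledge. Averaging in a null visit lowers power and shrinks the estimate. It also spends the baseline value, which could have removed variance, on diluting the effect. Utility is the endpoint that sets the sample size, so the stated 80% power of the trial rests on this step.

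**Working it through.** **Inputs (Sample size section).** Utility: f=0.1885976, N=140, m=4. Knowledge: f=0.2005347, N=134, m=3. Both use ρ=0.5 and α=0.05.

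**1. Reproduce the plan.** λ = f²·N·m / (1+(m−1)ρ), noncentral F with df 1 and N−2.
- Utility: 0.1885976²×140×4/2.5 = 7.967, power 0.800 (plan 0.8004).
- Knowledge: 0.2005347²×134×3/2 = 8.083, power 0.806 (plan 0.8058).

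**2. Set the Day 0 difference to zero**, with the full difference at every later visit. The averaged difference is (m−1)/m of the planned one, so λ is multiplied by ((m−1)/m)².
- Utility: 7.967×9/16 = 4.48, power **0.557**. For ρ=0.3 and 0.7 it is 0.67 and 0.47. With all 154 analysed it is 0.60. Reaching 0.80 needs N=248.
- Knowledge: 8.083×4/9 = 3.59, power **0.469**.

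A simulation of 20,000 trials per endpoint gave 0.558 and 0.463. The mean estimates were 0.750 and 0.664 of the true follow-up difference.

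**3. Knowledge effect size.** The plan's means give (1.70−1.39)/(2×0.648267) = 0.239, not 0.2005. The entered value implies a difference of 0.2005347×2×0.648267 = 0.26. With f=0.239, diluted power is 0.61 (N=134) or 0.63 (N=140), against 0.92 and 0.93 undiluted.

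**4. Other endpoints at N=140.** With the same 9/16 factor and the entered f, TNSS keeps 0.99 and VAS 0.95. The entered VAS f of 0.3245 is itself below the value from the plan's means, (85.5−72.1)/(2×13.251663) = 0.506, so 0.95 is not flattering. All three adherence measurements follow baseline, so adherence is not diluted.

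**5. Interaction reading.** λ = N·f²·((m−1)/m)/(1−ρ), numerator df m−1.
- Utility: 140×0.1885976²×0.75/0.5 = 7.47, power 0.62.
- Knowledge: 0.66 (f=0.2005, N=134) or 0.84 (f=0.239, N=140).

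**6. Follow-up mean adjusted for baseline (utility, N=140, k=3 follow-ups).** V = (1+(k−1)ρ_follow-up)/k − ρ_baseline², λ = N·f²/V, df 1 and N−3, N·f² = 4.98.

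| ρ_baseline | ρ_follow-up | V | λ | Power |
|---|---|---|---|---|
| 0.5 | 0.5 | 0.667−0.25 = 0.417 | 11.95 | 0.93 |
| 0.3 | 0.5 | 0.667−0.09 = 0.577 | 8.64 | 0.83 |
| 0.3 | 0.7 | 0.800−0.09 = 0.710 | 7.01 | 0.75 |

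The correlations of 0.3 and 0.7 are assumptions; the documents give only 0.5.

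**7. Within-group run.** λ = f²·N·m/(1−ρ) = 0.1005038²×138×4/0.5 = 11.15, df 3 and 408, power 0.806, as stated. This is the time effect pooled over both arms. For one arm of 69, λ = 5.58, df 3 and 204, power 0.48.

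**The case against.** **The analysis text never says main effect.** A two-way repeated-measures ANOVA also yields a group-by-time term. This stands as a caveat. The sizing runs are unambiguous, however, and wording about the mean difference between the arms' scores fits the main effect best. For utility the interaction also misses 80% at the plan's ρ of 0.5 (0.62), though it would reach 0.85 at ρ=0.7. For knowledge the choice matters: with f=0.239 the interaction meets 80%.

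**Knowledge power of 47% is not a settled figure.** This stands. It depends on an effect size that conflicts with the plan's own means, and on N=134 instead of the 140 planned as evaluable.

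**A reader might infer that the trial will probably miss a real benefit.** The documents do not support that. At 0.56, utility is detected slightly more often than missed. TNSS, VAS and adherence remain well powered on the plan's inputs. Nor is there a false-positive problem, since the arms are equal at Day 0 under the null as well.

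**The shrinkage might not show.** Means by visit may also be reported. The 25% or 33% therefore applies to any reported main-effect difference that includes baseline, not to every number in the report.

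**Adjustment does not guarantee 0.93.** This stands. Entry is restricted to moderate to severe disease and baseline precedes the intervention, so a lower baseline correlation is plausible, and power can then fall below 0.80.

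**Day 0 order.** Table 3 does not say that baseline questionnaires precede counselling. The calculation assumes that they do.

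**Conclusion.** The stated 80% power does not hold for the endpoint that sets the sample size. Utility has about 0.56 on the natural reading and 0.62 on the alternative, at the plan's own f, ρ and N=140. On the main-effect reading knowledge also falls short, at 0.47 to 0.63 depending on which effect size is used; the effect-size mismatch is a separate error. The power shortfall is confined to these two endpoints, while the dilution of the estimate also touches TNSS and VAS.

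The figures assume a zero expected Day 0 difference, a full effect from the first follow-up and one common correlation. An effect that builds up gradually to the planned difference would lower power further.

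As a secondary point, the 0.81 for within-group change describes a pooled time effect, whereas the secondary objective concerns change within each arm, for which it is about 0.48. That run uses a rule-of-thumb effect size, so it carries little weight.

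**What to change.** - For TNSS, EQ-5D utility, VAS and knowledge, replace the two-way ANOVA with a model whose outcomes are the follow-up visits only (Day 60, 120 and 180; Day 120 and 180 for knowledge). Use the baseline value as covariate, and group, visit and group-by-visit as effects.
- Name the between-group contrast in advance: the group difference averaged over follow-up visits, or the difference at Day 180.
- Rewrite the power statement for that contrast over a range of correlations. If the averaged contrast is chosen, the utility figures at N=140 are 0.93, 0.83 and 0.75, as tabulated above. A Day 180 contrast needs its own calculation.
- Correct the knowledge effect size, and check the VAS one, against the stated means.
- State that Day 0 questionnaires are completed before counselling, if that is the intention.
- Restate the within-group power per arm, or report within-arm changes as estimates with confidence intervals.

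The cost is wording in the Sample size and Statistical analysis sections. The data are already scheduled. Patients would be added only if the restated power were judged too low.

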### **Participant withdrawal & drop-out**

The participants are free to withdraw from the study at any time for any reason. For safety reasons, the participants may also be withdrawn from the study at any time at the discretion of the investigator. Reasons for withdrawal will be documented. The participant who withdrew will not be replaced. In the event of pregnancy, the patients will be instructed to inform the investigators and physician if she becomes pregnant during the study. Should the

913 participants become pregnant, she will be discontinued from the study. Since there is no  
914 investigational product is involved, the participants will not be follow up thereafter.

915 **Permitted and not permitted medications / treatments during trial**

916 This study did not involve any new investigational products or new invasive procedures or  
917 devices. Participants in the intervention will be exposed to educational materials and  
918 structured pharmacist counselling. Participants in both groups will continue to receive the  
919 usual care at the ENT outpatient clinic and pharmaceutical service at the outpatient  
920 pharmacy. There is no issue pertaining to the permitted or not permitted  
921 medications/treatments during this study. Participants are allowed to take all the prescribed  
922 medications; the over the counter medication consists of medication of interest  
923 (Antihistamine, Corticosteroids, Anticholinergics, Leukotriene receptor antagonists, Nasal  
924 saline, Decongestants, Beta- blocker) aimed to treat symptoms of allergic rhinitis that the  
925 participant purchased outside will be recorded.

926

927 There is no conclusive evidence to prove the use of traditional and complementary products  
928 improves allergic rhinitis significantly. The participants are allowed to take their traditional  
929 and complementary products as per their own routine.

930 **Rescue medication / procedure.**

931 The intervention group is receiving education materials as well as structured pharmacist  
932 counselling, and hence the risk of being exposed to unforeseeable risk is minimal. Should  
933 the participants have a flare-up of allergic rhinitis symptoms, they are advised to seek  
934 medical attention from the ENT outpatient clinic without waiting for their scheduled clinic  
935 appointment. If the patient's allergic rhinitis co-exists with asthma, they will be advised to go  
936 to the emergency & trauma department or primary health clinic nearest to them without  
937 waiting for their scheduled clinic visit. The participants will be advised to call the principal  
938 investigator after they have visited any health institution during out-of-schedule visits. They  
939 will be evaluated based on the date of their visit, the health care facility they went to, the  
940 medication they were prescribed, and the reason for their visit. They will also be graded for  
941 their allergic rhinitis status according to the ARIA guidelines and recorded in the assessment  
942 form at out-of-schedule visit at patient's nearest health institution (appendix D).

**Assessment of safety**

While there is no new investigational product or new invasive procedures, or new devices is involved in this study, there is no foreseeable adverse events related to the implementation of this pharmacist-led educational protocol. Should participants in the intervention group experience any side effect of the prescribed medication, it is unlikely due to the interventional approach introduced to them. Nevertheless, the medication side effects experienced by participants will be recorded in the assessment form (Appendix D).

If participants in both groups experience intercurrent illness or they find their symptoms getting worse, they are advised to come to the ENT outpatient clinic in this hospital, emergency & trauma department, or primary health clinic nearest to them without awaiting their scheduled clinic appointment. The participants will be advised to call the principal investigator after they have visited any health institution during out-of-schedule visits. They will be evaluated based on the date of their visit, the health care facility they went to, the medication they were prescribed, and the reason for their visit. They will also be graded for their allergic rhinitis status according to the ARIA guidelines and recorded in the assessment form at out-of-schedule visit at patient's nearest health institution (appendix D).

